### Outcomes

#### Primary Outcome

The primary outcome is the prevalence of cesarean delivery due to nonreassuring fetal status or the prevalence of neonatal acidosis. Neonatal acidosis will be defined as a UA pH <7.15 and a base excess greater than –12 mEq/L.

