### Management of SGA: Feto-Maternal Doppler

In recent years, and after the publication of DIGITAT, several studies have evaluated the role of feto-maternal circulation assessment by Doppler ultrasound in small fetuses [25-28]. These studies have shown that Doppler assessment allows identifying the subset of small fetuses at a higher risk of adverse perinatal outcomes (ie, those with FGR). Historically, umbilical artery (UA) pulsatility index (PI) assessed with Doppler has been considered the standard parameter to identify FGR. However, a large proportion of small fetuses with normal UA PI (ie, <95th percentile) have poorer perinatal outcomes than normally growing fetuses [21,29,30]. Thus, UA PI alone cannot be used to discriminate SGA from FGR fetuses [1,29]. Further studies showed that other Doppler parameters might have a greater predictive ability for adverse outcomes in late-onset SGA and FGR: cerebroplacental ratio (CPR), middle cerebral artery (MCA) PI, and uterine artery (UtA) PI [1,26,31,32]. According to these studies, abnormal CPR (ie, <5th percentile), MCA PI (ie, <5th percentile), or UtA PI (ie, >95th percentile) may be able to identify small fetuses at a higher risk of adverse outcomes (ie, FGR). A study including these criteria showed that small fetuses with abnormal Doppler parameters accounted for 60% of all small fetuses, indicating that more than half of fetuses with an EFW below the 10th percentile would be classified as FGR and that according to our current protocol, early-term induction of labor would therefore be recommended [25]. In the earlier study, induction of labor was recommended at 37 weeks of gestation in FGR fetuses (small fetuses with an EFW below the 3rd percentile or with an EFW below the 10th percentile accompanied by the presence of any abnormal Doppler parameter), while for other pregnancies with an EFW below the 10th percentile (ie, SGA fetuses) induction of labor was recommended at 40 weeks. Following that protocol, 134 cases (26.3%) had an adverse outcome, including, nonexclusively, 46 cases of neonatal acidosis and 106 cases of emergency cesarean delivery due to nonreassuring cardiotocography (CTG). Neonatal acidosis in that study was defined as a UA pH below 7.15 and a base excess greater than –12 mEq/L.

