### Rationale for the Study

The most common protocols used worldwide for the management of late-onset SGA/FGR are based on Doppler assessment, which recommends elective delivery at 37 weeks (or even earlier) in FGR pregnancies [25,37,38]. According to a classification based on Doppler parameters and EFW percentiles, up to 79.1% of small fetuses would be classified as FGR. By contrast, when using the AF-based approach (sFlt-1/PlGF ≥38), only 19.6% of small fetuses would be classified as FGR [36]. Additionally, both approaches seem to have a similar ability to identify small fetuses at risk (ie, those with FGR), which may benefit from an earlier elective delivery. Therefore, the AF-based protocol may potentially reduce by up to 75.2% (from 79.1% to 19.6%) the number of pregnancies classified as FGR (in which labor would be induced at 37 weeks) without worsening perinatal outcomes. Moreover, reducing the number of unnecessary labor inductions would not only improve patients’ perception of medical attention, but also would reduce the costs and risks derived from possible iatrogenic complications, which in turn would reduce the rate of cesarean deliveries. Additionally, fewer inductions would lower the rate of early-term neonates, thus improving neonatal outcomes and potentially reducing long-term infant metabolic, endocrine, and respiratory morbidities.

The sFlt-1/PlGF ratio has been shown to accurately predict PE and associated complications several weeks before onset [39-42]. Therefore, a management protocol based on AFs may potentially reduce the rate of PE and other maternal complications associated with PE, such as placental abruption or eclampsia.

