### Objectives

#### Primary Objective

To determine whether the classification of small fetuses as FGR or SGA based on AFs is not inferior to the standard clinical approach (based on EFW and Doppler percentiles) for the identification of fetuses at a higher risk of adverse perinatal outcomes (neonatal acidosis and cesarean section due to nonreassuring CTG).

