#### Secondary Objectives

To determine whether (1) the lower false-positive rate using AFs instead of Doppler to identify small fetuses as FGR results in a reduced number of elective deliveries before 38, 39, and 40 weeks, (2) a lower rate of early-term elective deliveries results in a reduced number of deliveries (elective and spontaneous) before 38, 39, and 40 weeks, (3) a lower rate of early-term elective deliveries results in a reduced number of cesarean deliveries, (4) a lower rate of early-term elective deliveries results in a reduced number of neonatal admissions to the NICU and a lower rate of adverse perinatal outcomes, (5) the AF-based approach reduces PE incidence in pregnancies with small fetuses, and (6) the AF-based classification reduces the incidence of placental-related complications.

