#### Secondary Outcomes

Composite adverse perinatal outcome will be defined as the presence of at least one of the following: fetal death, Apgar score <7 at 5 minutes, UA pH <7.05, admission to the NICU or a transitional care unit within 48 hours, birthweight <2000 grams, maternal admission to the obstetric intensive care unit within 48 hours (before or after delivery), and PE.

Composite adverse neonatal outcomes will be defined as the presence of at least one of the following: respiratory distress syndrome (respiratory rate >60 or <30 breaths/min, grunting on expiration, chest indrawing, central cyanosis, apnea, or the need for surfactant therapy in the neonatal period) [62], transient tachypnea, required ventilatory support, grade III or IV intraventricular hemorrhage, neonatal sepsis, hypoglycemia, necrotizing enterocolitis, neonatal jaundice (treated with phototherapy), neonatal seizures, pneumonia, meningitis, and neonatal death.

Other secondary outcomes will include the following: rates of elective delivery before 38, 39, and 40 weeks of gestation; rates of deliveries (elective and spontaneous) before 38, 39, and 40 weeks of gestation; rate of birthweight <2500 grams; rate of UA pH <7.10; rate of elective cesarean delivery; rate of cesarean delivery due to failed labor induction; rate of emergency operative vaginal delivery; and rate of placental-related complications, such as placental abruption, pregnancy hypertension, severe PE, eclampsia, stroke, maternal death, and postpartum hemorrhage.

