### Sample Size

A management protocol based on EFW and Doppler assessment has shown a prevalence of adverse perinatal outcomes of 26%, meaning that there is a prevalence of 74% of pregnancies with no complications [25]. The estimated rate of pregnancies with no complications in the intervention group has been set at 74%, with a lower limit of 65.5% (a maximum achievable difference of 8.5%). Based on these considerations and an estimated dropout rate of 3%, the sample size needed for a noninferiority design with a power of 80% and a significance level of 5% is 1030 participants, that is, 515 in each group. Noninferiority will be demonstrated if the lower limit of the 95% CI of the difference between incidences of pregnancies without neonatal acidosis is less than –8.5%. If the dropout rate is greater than 3%, the number of participants will be increased so as to achieve 1000 participants with complete data for the primary outcome.

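### The primary outcome counts cesarean but not operative vaginal delivery for nonreassuring fetal status, so a difference between arms in rescue route could move the event rate without any change in fetal compromise

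*Protocol article*

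**What the plan says.** The Primary Outcome section of the protocol article defines the endpoint as follows: "The primary outcome is the prevalence of cesarean delivery due to nonreassuring fetal status or the prevalence of neonatal acidosis". For the second component it adds "Neonatal acidosis will be defined as a UA pH <7.15", together with a base excess criterion. Acidosis counts whatever the mode of delivery. The Primary Objective and the Discussion name the same two components.

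Instrumental delivery appears once among the outcomes, under Secondary Outcomes, as "rate of emergency operative vaginal delivery". It is not split by indication and belongs to neither secondary composite. The Intervention section gives indications for elective and intrapartum cesarean but none for operative vaginal delivery. Nonreassuring CTG before and during labor is defined under Predictive Variables.

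The strategies differ in when labor starts. Under Intervention, fetuses classified as FGR are recommended for delivery from 37 weeks, while those classified as SGA wait until 40. The introduction expects about 79.1% to be classified as FGR by Doppler and 19.6% by angiogenic factors. The Rationale expects fewer inductions, "which in turn would reduce the rate of cesarean deliveries", and a secondary objective asks whether "a lower rate of early-term elective deliveries results in a reduced number of cesarean deliveries". The section on randomization and masking says that participants, investigators and outcome assessors will all know the allocation.

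**The concern.** Cesarean and instrumental delivery are two ways to end a labor because of a worrying tracing, and the composite counts only one of them. Which one is used depends partly on how far labor has advanced, not only on the condition of the fetus. Two nonacidotic neonates delivered for the same tracing are scored as a failure and a success if one is born by cesarean and the other instrumentally.

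The trial compares strategies that change gestational age at delivery and the proportion of induced labors, with the treating staff aware of the arm. Rescue route could therefore differ between arms for reasons other than fetal compromise. In a noninferiority comparison, events that become non-events in the intervention arm push toward the claim, and events added in that arm push against it. The stand-alone instrumental rate would show a large shift, but not how many of those deliveries were for nonreassuring CTG, and it does not enter the noninferiority decision.

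**Working it through.** **Inputs.** The section on feto-maternal Doppler reports 134 adverse outcomes (26.3%) in the source cohort, comprising, nonexclusively, "46 cases of neonatal acidosis and 106 cases of emergency cesarean delivery due to nonreassuring cardiotocography". Sample Size gives a control event rate of 26%, a margin of 8.5 points and a target of 1000 women with complete data, so 500 per arm at 1:1. The decision uses a 95% CI, taken here as two-sided (one-sided 2.5%). No rate of operative vaginal delivery is given.

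**The plan's own figures.** The cohort size implied by 134 at 26.3% is 134/0.263 = 509.5, about 510, which agrees with the 26% used for sample size. That rate is therefore the composite rate. The total of 1030 does not reproduce: 2 × 0.74 × 0.26 × (1.960 + 0.842)² / 0.085² gives 419 per arm, 838 in total, and 864 after 3% dropout. The stated number is larger than its inputs require. Nothing below depends on this, since 500 completers per arm are taken as planned.

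**Which events can disappear.**
- Cases with both components: at least 106 + 46 − 134 = 18.
- Cesarean without acidosis: at most 106 − 18 = 88, which is 88/134 = 66% of events and 88/510 = 17.3% of women.
- A cesarean with acidosis stays an event whatever the route, so 17.3% is the ceiling of what a change of route can remove.

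**Size of a shift (assumed 10% to 25% of these cesareans).**
- 0.10 × 17.3 = 1.7 points.
- 0.25 × 17.3 = 4.3 points.

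**Effect on the decision.** With control rate p_c = 0.26, true excess d in the intervention arm and shift s away from cesarean in that arm, the observed rate is p_t = 0.26 + d − s. The standard error is SE = √[p_c(1−p_c)/500 + p_t(1−p_t)/500], and P(noninferior) = Φ[(0.085 − (p_t − p_c))/SE − 1.96].

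| True excess d | Shift s (points) | p_t | SE | P(noninferior) |
|---|---|---|---|---|
| 0 | 0 | 0.260 | 0.0277 | 86.5% |
| 0 | 1.7 | 0.243 | 0.0274 | 96.1% |
| 0 | 4.3 | 0.217 | 0.0269 | 99.7% |
| 0 | −1.7 (toward cesarean) | 0.277 | 0.0280 | 68.0% |
| 0 | −4.3 (toward cesarean) | 0.303 | 0.0284 | 31.5% |
| 8.5 points | 0 | 0.345 | 0.0289 | 2.5% |
| 8.5 points | 1.0 | 0.335 | 0.0288 | 5.3% |
| 8.5 points | 1.7 | 0.328 | 0.0287 | 8.6% |
| 8.5 points | 4.3 | 0.302 | 0.0284 | 32.8% |

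A shift away from cesarean raises the chance of a false noninferiority claim. A shift toward it costs power.

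**Precision of a broader composite.** If instrumental delivery for nonreassuring CTG without acidosis adds the same number of points in both arms (assumed 2, 5, 10 or 15), power against 8.5 points with 500 per arm is 84.9%, 82.8%, 80.0% and 78.0%. The 95% CI half-width with no true difference goes from 5.4 points with nothing added to 6.0 at 10 added points (1.96 × √[2 × 0.64 × 0.36/500]).

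**The case against.** The strongest reply is that this is a choice and not an error. The components are the same in the objective, the outcome section and the Discussion, and they match the cohort that supplied the 26%. Acidosis counts regardless of route, so measured compromise is captured directly. Emergency operative vaginal delivery is itself compared between arms with differences, relative risks and 95% CIs, as are lower pH thresholds, Apgar score and NICU admission within their composites or alone. The indication for instrumental delivery may well be on the case report form, which is not shown. All of this stands. It limits the size and urgency of the point, but it does not let the reported results separate fewer compromised fetuses from a changed rescue route.

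A reader might infer that the protocol itself predicts substitution in favour of the new strategy. It does not. The Rationale and the secondary objective expect fewer cesareans overall, which includes those for failed induction and prolonged labor. Neither says that rescue moves from cesarean to instrumental delivery, and a fall in cesareans for nonreassuring CTG could be real benefit.

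A reader might also apply the assumed shift to all 106 cesareans (106/510 = 20.8% of women) and obtain 2.1 to 5.2 points. That is too large, because at least 18 of the 106 neonates were also acidotic and would remain events. Even the 88 is a ceiling, since a cesarean performed before instrumental delivery is feasible could not have changed route.

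**Conclusion.** The point holds as a limited design weakness. Under the stated composite, a nonacidotic neonate delivered instrumentally for nonreassuring fetal status is a success and one delivered by cesarean is a failure, in an open-label trial whose arms differ by design in timing and onset of labor. An assumed 10% to 25% change of route moves the event rate by at most about 1.7 to 4.3 points, that is, 20% to 51% of the 8.5-point margin (1.7/8.5 and 4.3/8.5).

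This rests on the source cohort's component counts carrying over to the trial and on a shift fraction for which the documents offer no anchor. The documents do not establish that a shift will occur or in which direction, so a claim that the primary result is biased toward noninferiority would go too far.

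The point also depends on the composite being what is tested. Sample Size words the decision rule in terms of pregnancies free of neonatal acidosis only, although its 26% is the composite rate. If acidosis alone were tested, cesarean would not count either and this mechanism would vanish. The two sections must be reconciled.

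**What to change.** Leave the primary outcome as it is. Then:

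- Identify which operative vaginal deliveries were done for nonreassuring CTG, using the definition already given under Predictive Variables, and report the secondary instrumental rate by that indication.
- Prespecify one supportive sensitivity analysis of cesarean or operative vaginal delivery for nonreassuring CTG, or neonatal acidosis. Report its difference and 95% CI beside the primary result. A woman who moves from one rescue route to the other stays an event in this composite, so a gap between the two analyses shows how much of the primary result reflects route.
- Do not make agreement of this analysis a condition for noninferiority. The 8.5-point margin was set for the 26% composite, the documents give no control rate for the broader one, and requiring both would lower power.
- Align the decision rule under Sample Size with the composite in the Primary Outcome section.

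The cost is one indication field, if it is not already collected, and one extra analysis with a somewhat wider interval because the event rate is higher. The broader composite also adds an event that depends on the decision of unmasked clinicians, which is a further reason to keep it supportive.

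### As worded, the acidosis component of the primary outcome counts base excess above –12 and rejects –12 or lower; direction and boundary need to be stated

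*Protocol article*

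**What the plan says.** The Primary Outcome section of the protocol article sets a two-part composite: "The primary outcome is the prevalence of cesarean delivery due to nonreassuring fetal status or the prevalence of neonatal acidosis". It then defines the second part: "Neonatal acidosis will be defined as a UA pH <7.15 and a base excess greater than –12 mEq/L". The two laboratory conditions are joined by 'and', so both must hold.

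The background section on feto-maternal Doppler uses the same wording for the study that supplies the planning rate: "Neonatal acidosis in that study was defined as a UA pH below 7.15 and a base excess greater than –12 mEq/L". That study's counts are given there: "134 cases (26.3%) had an adverse outcome, including, nonexclusively, 46 cases of neonatal acidosis and 106 cases of emergency cesarean delivery". The Sample Size section takes its 26% adverse-outcome rate from this study.

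The Secondary Outcomes section uses two other pH thresholds, neither with a base-excess condition. One stands inside the composite adverse perinatal outcome ("fetal death, Apgar score <7 at 5 minutes, UA pH <7.05") and one stands alone ("rate of UA pH <7.10").

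The article nowhere mentions base deficit or an absolute value, and nothing else in it shows which side of –12 is meant.

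**The concern.** The threshold carries its minus sign, so a base excess greater than –12 means –11.9, –5, 0 and so on. Joined to pH below 7.15, the rule selects newborns with a low pH and a modest base deficit. It leaves out of the acidosis component those with the same or lower pH and a large base deficit. For an outcome labelled neonatal acidosis, that ordering runs the wrong way.

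The wording matters because it defines an event in the primary outcome of a noninferiority trial. Coded from the text, the event would be assigned in the opposite direction from the one that the label suggests. Read by people at 20 sites, the phrase could be applied in both directions. It also leaves unclear which endpoint the 26% planning rate describes.

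**Working it through.** **1. Apply the rule as written and the rule with the inequality reversed.** Inputs: pH below 7.15 with base excess (BE) above –12, as in the Primary Outcome section; the same pH condition with BE below –12; and the two pH cut-offs from Secondary Outcomes. The cord-gas values are illustrations, not trial data.

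| UA pH | BE (mEq/L) | Acidosis, as written | Acidosis, reversed | pH <7.10 | pH <7.05 |
|---|---|---|---|---|---|
| 7.14 | –2 | yes | no | no | no |
| 7.12 | –8 | yes | no | no | no |
| 7.10 | –11.9 | yes | no | no | no |
| 7.08 | –12 | no | no | yes | no |
| 7.05 | –13 | no | yes | yes | no |
| 6.98 | –16 | no | yes | yes | yes |
| 6.95 | –18 | no | yes | yes | yes |

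No newborn counts under both rules, so the difference is not a small shift of a cut-off. A value of exactly –12 counts under neither, because both inequalities are strict. Under the wording as it stands, a newborn at pH 6.98 and BE –16 is an adverse perinatal outcome in the secondary composite but not an acidosis event in the primary outcome. A newborn at pH 7.14 and BE –2 is the reverse.

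**2. Find the part of the composite that depends on this definition.** Inputs from the background section: 134 adverse outcomes (26.3%), 46 acidosis cases and 106 emergency cesareans for nonreassuring cardiotocography.

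- Implied denominator: 134 / 0.263 = 509.5, about 510. Check: 134 / 510 = 26.3%, which agrees with the article and with the rounded 26% in Sample Size.
- Overlap, if these are the only two components: 46 + 106 – 134 = 18 newborns with both, or 18 / 46 = 39% of the acidosis cases.
- Acidosis without such a cesarean: 46 – 18 = 28.
- Share of events: 28 / 134 = 20.9%. Share of pregnancies: 28 / 510 = 5.5%.

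If the source composite had further components, acidosis and cesarean together would cover fewer than 134 cases. The overlap would then exceed 18, so 28 is the largest value that these counts allow.

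**3. Consider what the source study may have used.** The article does not settle this, so there are two cases.

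- If the 46 cases were defined by BE below –12, a literal derivation would count none of them as acidosis. On the two-component assumption, 106 / 510 = 20.8% of pregnancies would remain as events, plus an unknown number of newborns with pH below 7.15 and BE above –12. The 26% rate would then describe a different endpoint.
- If the 46 cases were defined literally, none of the 28 would be at –12 or lower, and the planning rate would match the trial's text.

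The article gives no base-excess distribution, so neither the number misclassified nor the net change in the event rate can be calculated.

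**The case against.** The strongest reply is that this is loose wording. The label is neonatal acidosis, the same phrase is used for the source study, and many readers would take it to mean a base deficit above 12. The repetition also makes the planning rate and the trial endpoint nominally consistent. Harm follows only if someone codes the phrase literally, and nothing shows that this was done. Most of that stands: shorthand is the likely explanation. But it is an inference that the article does not confirm, and repeating the phrase does not correct its direction. A condensed article may omit detail; that does not cover a definition that is stated and reads the wrong way.

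Three stronger readings are tempting and are not supported.

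- A reader might infer that newborns at –12 or lower are excluded from the primary outcome altogether. They are excluded only from its acidosis component. Those delivered by cesarean for nonreassuring fetal status still count, as 18 of the 46 source-study acidosis cases would if there were only two components. The secondary pH outcomes also keep the lowest pH values visible in the results, although they do not repair the primary outcome.
- A reader might take the 28 cases as the number misclassified. They are all the acidosis-only events. The misclassified number could be zero or most of them, depending on a definition and a distribution that the article does not give.
- A reader might infer that the lost events are those most likely to separate the arms. Nothing in the article shows that acidosis with a large base deficit would differ between arms more than milder acidosis or cesarean for nonreassuring cardiotocography.

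**Conclusion.** The point holds as a defect in the wording of a primary-outcome component. Taken as written, the rule puts newborns with pH below 7.15 on the wrong side of –12 for an outcome called acidosis, and it leaves exactly –12 unaddressed if the direction is simply reversed. It should be corrected before the primary outcome is derived, whatever the intent.

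The size is bounded only loosely. Assuming a two-component source composite and about 510 pregnancies, roughly one composite event in five rests on this definition alone. The effect on the noninferiority conclusion cannot be stated, and no bias for or against either arm has been shown.

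**What to change.** Amend the definition in the Primary Outcome section so that direction and boundary cannot be misread: base excess more negative than –12 mEq/L, that is, a base deficit above 12, with an explicit statement of whether exactly –12 counts. Before adopting it, confirm that it matches the definition that produced the 46 source-study cases, so that the 26% planning rate still applies. If it does not match, the planning rate needs to be restated for the definition chosen. Correct the matching sentence in the background section in the light of that check.

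Derive the event by program from recorded pH and signed base excess, with one rule for all sites, rather than from a site's own judgement of acidosis. Check at data entry that base excess is stored with its sign and not as a base deficit.

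The cost is a one-line amendment and one derivation check. Both measurements are already needed for the outcome, so no new data collection is required unless a site has recorded acidosis only as present or absent. The article does not say how it is recorded; in that case the cord-gas values would have to be retrieved.
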